**AMENDMENTS**

The following amendments and/or administrative changes have been made to this protocol since the implementation of the first approved version.

| Amendment number | Date of amendment | Protocol version number | Type of amendment | Summary of amendment |
| --- | --- | --- | --- | --- |
|  |  |  |  |  |
|  |  |  |  |  |
|  |  |  |  |  |

**Trial Synopsis**

| CORRECT | COmbination of Radiotherapy with anti-PD-1 antibody for unREseCtable inTrahepatic cholangiocarcinoma | | | |
| --- | --- | --- | --- | --- |
| Chief Investigator | [name] | | | |
| Registration No. | NCT03898895 | Sponsor | The First Affiliated Hospital, Sun Yat-sen University | |
| Trial Aim | Investigate the efficacy and safety of radiotherapy combined with anti-PD-1 antibody for unresectable intrahepatic cholangiocarcinoma. | | | |
| Trial Design | Open label, single-arm phase II clinical trial | | | |
| Phase II trial | Primary Endpoint:   - 1-year progression-free survival (PFS) rate | | | Secondary Endpoints:   - Overall survival (OS) - Adverse events (AE) - Objective response rate (ORR) - Disease control rate (DCR) |
| Patient Population and Sample Size | 36 patients with unresectable intrahepatic cholangiocarcinoma. | | | |
| Key Entry Criteria | | | | |
| *Inclusion* | - Age: 18-75 years; - Histopathologically confirmed unresectable primary or postoperative recurrent intrahepatic cholangiocarcinoma without distant metastasis; - No previous radiotherapy or systemic therapy; - Adequate volume of the uninvolved liver (larger than 700 mL); - At least one measurable lesion based on RECIST 1.1 criteria; - ECOG PS 0-1; - Adequate hematologic, hepatic and renal function: ANC ≥ 1.5x10^9/L, Hb ≥ 90g/L, PLT ≥ 100 x10^9/L, albumin ≥ 28g/L, total bilirubin < 1.5×ULN at diagnosis or after biliary drainage, ALT and AST < 5×ULN, BUN and CREA<1.5×ULN, creatinine clearance rate ≥ 45ml/min; - Life expectancy of at least 12 weeks. | | | |
| *Exclusion* | - Have acute or chronic active hepatitis B or C, HBV-DNA＞2000IU/ml or 10^4^ copy/ml; HCV-RNA＞10^3^ copy/ml; both HBsAg and HCV antibody are positive. If the related results become lower than above standards after antiviral treatment, the patients are qualified for enrolment; - Have distal or perihilar cholangiocarcinoma, gallbladder cancer or carcinoma of the ampulla of Vater; have metastasis in extrahepatic distant organs including lung, central nervous system, bone and etc., or extrahepatic lymph node metastasis beyond abdomen; - Have risky bleeding events requiring transfusion, operation or local therapies, continuous medication in the past 3 months; - Have thromboembolism in the past 6 months, including myocardial infarction, unstable angina, stroke or transient ischemic attack, pulmonary embolism, deep vein thrombosis; - Have taken aspirin (＞325mg/day) or other antiplatelet drugs continuously for 10 days or more within 2 weeks before enrolment; - Uncontrollable hypertension, systolic pressure＞140mmHg or diastolic pressure＞90mmHg after best medical care, or history of hypertensive crisis or hypertensive encephalopathy; - Symptomatic congestive heart failure (NYHA class II-IV). Symptomatic or badly-controlled arrhythmia. Congenital long QT syndrome or modified QTc＞500ms upon screening; - Have active autoimmune diseases that require systemic treatment within 2 years before enrolment; - Active tuberculosis, having antituberculosis therapy at present or within 1 year; - Have a known history of prior invasive malignancies within 5 years before enrolment; - Pregnant or breastfeeding women, or expecting to conceive or father children within the projected duration of the trial; - Have other uncontrollable comorbidities; - Infection of HIV, known syphilis requiring treatment; - Allergic to elements of camrelizumab. | | | |
| Trial Treatment & Assessments | | | | |
| Single-armed phase II trial | - The total radiation dose is over 45Gy without damaging organic function. Conventional intensity-modulated radiotherapy or stereotactic body radiation therapy are both allowed. Camrelizumab 200mg intravenously every 3 weeks will be initiated within 7 days after radiotherapy. Patients will receive camrelizumab until clinical or radiographic disease progression, unacceptable toxicity, death or withdrawal. - Tumor response using contrast-enhanced computed tomography or magnetic resonance imaging should be first performed every 6 weeks. | | | |

**1. Background and rationale**

**1.1 Epidemiology of intrahepatic cholangiocarcinoma**

Cholangiocarcinoma (CCA) is the second most common hepatic malignancy after hepatocellular carcinoma (HCC), and the overall incidence of CCA, especially the intrahepatic cholangiocarcinoma (iCCA) has increased progressively worldwide over the past four decades (1-3). Multiple studies reported that the incidence of ICC increased by up to 10-fold over a 3-decade period around the turn of the 20th century in Australia, Japan, the USA, the UK, and across Europe (4). Surgery is the first-line and only curative treatment option for resectable iCCA. However, only approximately 30%-40% of biliary tract cancer patients are amenable to surgical resection (5). The median survival is only 3.3 months in patients with unresectable iCCA who only received supportive therapy (6).

**1.2 Current treatment of unresectable intrahepatic cholangiocarcinoma**

Considering the dismal prognosis, the National Comprehensive Cancer Network (NCCN) guideline recommends several treatment options for patients with unresectable iCCA. Current recommended therapies include gemcitabine-cisplatin combination therapy, fluoropyrimidine-based therapy, gemcitabine-based therapy, external beam radiation therapy (EBRT) combined with concurrent fluoropyrimidine, locoregional therapies, immunotherapy and targeted therapy. Among these recommendations, gemcitabine-cisplatin combination therapy is recommended with the highest-level evidence. Many clinical trials support the fluoropyrimidine-based and gemcitabine-based therapies. However, the benefit of EBRT with concurrent fluoropyrimidine, locoregional therapies, immunotherapy and targeted therapy in unresectable iCCA is not defined due to limited clinical trial data.

Valle J et al. conducted a phase III RCT to evaluate the efficacy and safety of gemcitabine-cisplatin combination therapy versus gemcitabine alone for 410 patients with unresectable, recurrent or metastatic biliary tract cancer (7). 80 patients were with iCCA in the study. They reported a median overall survival (OS) of 11.7 months in the combination group and 8.1 months in the gemcitabine-alone group (*P*<0.001). The median progression-free survival (PFS) was 8.0 months in the combination group and 5.0 months in the gemcitabine-alone group (*P*<0.001). In addition, the rate of tumor control among patients in the combination group was significantly increased (81.4% vs. 71.8%, *P* = 0.049). The rate of grade 3 or 4 toxic effects was 68.8% in the combination group. An alternative therapy of combination of gemcitabine and nab-paclitaxel was investigated by Sahai V et al. in 2018 (8). They enrolled 74 patients with advanced or metastatic CCA including 61 iCCA cases. The study demonstrated an OS of 12.4 months, a PFS of 7.7 months and a disease control rate (DCR) of 66%. Adverse events (grade 3 or higher) were reported in 57% of cases.

Due to the limited survival benefit and nonnegligible adverse events of gemcitabine-based chemotherapies, there is a necessity of developing other therapies to relieve the situation. Besides, since the biology of gallbladder cancer, iCCA and extrahepatic cholangiocarcinoma are distinct (5), iCCA should be separately studied in clinical trials.

**1.4 Safety and efficacy of anti-PD-1 antibodies in unresectable intrahepatic cholangiocarcinoma**

Programmed death 1(PD-1) is one of the immune checkpoint receptors expressed by activated T cells. The interaction between PD-1 and its ligands, PD-L1, can promote a series of changes and cause exhaustion of T cell, which leads to immune escape of tumor cells (16, 17). Antibodies against PD-1 or PD-L1 have been reported to have valid antitumor activity and safety in varied kinds of carcinoma, including melanoma, lung cancer and HCC (18, 19).

Recently, Sarina et al. summarized the clinical trial results of pembrolizumab as a therapy for advanced biliary tract cancer (20). The study achieved a median PFS of 2.0 months and median OS of 7.4 months in 128 patients. Although the OS was short, it was still satisfying since most of the treated patients were at a late treatment stage whose expected survival was about 3 months with best supportive care. The rate of grade 3 or 4 adverse events was lower than 17% (21). Several clinical trials on checkpoint inhibitors treating CCA are still under evaluation, all of which focused on advanced stage patients (22).

**1.5 Safety and efficacy of radiotherapy combined with anti-PD-1 antibodies for unresectable intrahepatic cholangiocarcinoma**

Preclinical animal experiments have confirmed that radiotherapy combined with anti PD-1/PD-L1 antibodies can achieve synergistic enhancement of immune efficiency (23, 24). There has been an increase of studies evaluating radiotherapy combined with anti PD-1/PD-L1 antibodies. The combination therapy has been studied in 73 patients with metastatic solid tumors including 6 CCA and the patients underwent a median of 5 prior therapies (25). Outcomes were as follows: ORR was 13.2%, OS and PFS were 9.6 and 3.1 months. The rate of grade 3 or 4 adverse events was only 8.2%. Besides, there was a low incidence of hepatobiliary toxicity and no dose-limiting toxicity occurred in liver metastases. Previous studies of other tumor types have verified that the incidence of adverse events of combination therapy is acceptable and similar to that of anti PD-1 antibodies monotherapy, and fatal complications are rare (23, 25, 26).

**2. Objectives and endpoints**

**2.1 Objectives**

Investigate the efficacy and safety of radiotherapy combined with anti-PD-1 antibody for unresectable intrahepatic cholangiocarcinoma.

**2.2 Primary endpoint**

**1-year progression-free survival (PFS) rate**: defined as the rate of patients free of progressive disease at one year according to RECIST 1.1. Progression-free survival (PFS) was defined as the time from the commencement of radiotherapy until disease progression or death from any cause, whichever happens first. Patients who withdraw or who are lost to follow-up will be censored at the date of the last adequate tumor assessment. Patients not having an event will be censored at the date of the last adequate tumor assessment. If patients don’t have baseline tumor assessments, they will be censored at the date of the first treatment.

**2.3 Secondary endpoints**

**Overall survival (OS)**: defined as the time from the commencement of radiotherapy until death from any cause. Patients who withdraw or are lost to follow-up or still alive will be censored at the date last known to be alive.

**Adverse events (AE)**: adverse events during the treatment period using Common Terminology Criteria for Adverse Events (CTCAE) (version 5.0).

**Objective response rate (ORR)**: defined as the proportion of participants with a complete response or partial response according to the Response Evaluation Criteria in Solid Tumors (RECIST) criteria 1.1.

**Disease control rate (DCR)**: defined as the proportion of participants with a complete response, partial response, or stable disease according to the RECIST criteria 1.1.

**2.4 Exploratory endpoints**

Antitumor activity assessed by following biomarkers will be explored, but more biomarkers should be tested if necessary.

**T-cell–inflamed gene-expression profile (GEP) analysis:** tumor RNA extracted from pretreatment formalin-fixed paraffin-embedded slides will be analyzed and GEP score was calculated as a weighted sum of normalized expression values for the 18 genes.

**Tumor mutational burden (TMB)**: total DNA was extracted from the snap-frozen tissues. TMB, considered as numbers of mutations per megabase (Mb) of genome examined.

**Expression of PD-L1:** assessed in pretreatment samples by 22C3 immunohistochemistry (IHC) staining. PD-L1 positive status was defined as staining in ≥1% of tumor cells or presence of staining of any intensity in tumor-infiltrating immune cells at any intensity.

**Genomic alterations**: including microsatellite stability status, nucleotide variants, short and long insertions and deletions, copy number variants, and gene fusions were assessed.

**Mismatch repair deficiency (MMR)/ microsatellite instability (MSI)**: DNA will be extracted from slides of formalin-fixed and paraffin-embedded tumor and matched normal samples. The size in bases is determined for each microsatellite locus and tumors are designated as MSI if two or more mononucleotide loci vary in length compared to the germline DNA.

**3. Design**

This is an open label, single-arm phase II clinical trial.

The total radiation dose is over 45Gy without damaging organic function. Conventional intensity-modulated radiotherapy or stereotactic body radiation therapy are both allowed. Camrelizumab 200mg intravenously every 3 weeks will be initiated within 7 days after radiotherapy. Patients will receive camrelizumab until clinical or radiographic disease progression, unacceptable toxicity, death or withdrawal. Considering the possibility of pseudoprogression, patients with initial judgment of disease progression were treated with an additional 200 mg of camrelizumab, and radiologic examination was performed 4 weeks later to confirm whether it was pseudoprogression or disease progression. If it is true, the camrelizumab should be stopped.

A total of 36 patients will be recruited. The expected recruitment duration is 24 months. After the treatment, the patients will be followed up until progression, death, or termination of the study for patient withdrawal.

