**4 Follow-up**

**4.1 Timeframe**

Tumor response using contrast-enhanced computed tomography or magnetic resonance imaging should be performed every 6 weeks. Physical examination and hematological tests (complete blood count, liver function, biochemical tests) should be perform each week during radiotherapy, then every 3 weeks since the initiation of camrelizumab.

During each follow-up, patients are allowed to arrange their visits flexibly in a predefined 7-day timeframe. For example, a patient is required to visit on day 10, he or she is free to make the visit between day 7 and day 13.

Each patient should insist on a predefined specific type of imaging during follow-up. For patients contraindicated for MRI imaging due to metal implants or other reasons, CT should be performed continuously during each follow-up.

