**8.2 Treatment discontinuation**

In the event of discontinuation of trial treatment, full details of the reason(s) for discontinuation should be recorded in the patient’s medical notes and on the appropriate pages on the Case Report Form (CRF). All patients, including non-compliant subjects, should be followed up according to the protocol unless they withdraw consent.

A patient should discontinue the trial drug in the event of any of the following:

• Disease Progression (Radiological disease progression, Clinical disease progression

• Unacceptable toxicity

• Any other adverse event which, in the Investigator’s opinion, requires termination of the trial medication

• Administration of any other anti-tumor therapies during the trial

• Pregnancy

• Any other reason given by the Investigator

• The patient uses illicit drugs or other substances that may, in the opinion of the Investigator, have a reasonable chance of contributing to toxicity or otherwise interfering with results

• The development of a second malignancy that requires treatment

• Request by the patient or a legal representative/relative to stop the treatment

• Death or End of Trial

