**10. Data handling and record keeping**

**10.1 Data collection**

The CRF must be completed, signed/dated and returned to the CORRECT Trial Office by the Investigator or an authorized member of the site research team (as delegated on the Site Signature and Delegation Log) within the timeframe listed below in Table 1. The exception is the SAE Form, which must be co-signed by the Investigator. See AE reporting Section 8.2 for further details.

Table 1: The Case Report Forms (CRFs)

| Case Report Form | Timelines for completion & return to Trial office |
| --- | --- |
| Baseline Assessment Form | Complete prior to treatment |
| Eligibility Checklist | Complete during screening and return immediately following recruitment of the patient |
| Treatment form | Complete the form at the end of each cycle. |
| Follow-up form | Complete after each treatment cycle |
| Adverse Event Monitoring Form | Complete at baseline (i.e. immediately after recruitment) and on completion of each treatment cycle (as per treatment form) |
| Concomitant Medication Form | Complete at baseline (i.e. immediately after recruitment) and on completion of each treatment cycle (as per treatment form) |
| Treatment Discontinuation Form | Complete when the patient finishes treatment regardless of cause |
| SAE Form | Complete the form within 24h of first awareness of the event and fax to the Trials Office immediately (See section 8.2) |
| Relapse Form | Complete immediately upon patient relapse |
| Death Form | Complete immediately upon notification of patient’s death |
| Pregnancy Notification Form | Complete immediately on being notified of patient pregnancy |
| Deviation Form | Complete immediately upon discovering deviation |
| Withdrawal Form | Complete immediately upon patient withdrawal |

Entries on the CRF should be made in ballpoint pen, in blue or black ink, and must be legible. Any errors should be crossed out with a single stroke, the correction inserted and the change initialed and dated. If it is not obvious why a change has been made, an explanation should be written next to the change.

Data reported on each form should be consistent with the source data or the discrepancies should be explained. If information is not known, this must be clearly indicated on the form. All missing and ambiguous data will be queried. All sections are to be completed before returning to the CORRECT Trial Office.

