**13.3 Statistical methods**

PFS and OS will be analyzed by the Kaplan-Meier method for all patients, and compared by the log-rank test for different TMB, PD-L1 and microsatellite status subgroups.

Adverse events will be summarized based on frequency and proportion of all patients. The summaries with descriptive statistics will be given for AEs by any toxicity grade, grade 3 or higher AEs, SAEs and AEs leading to discontinuation of study treatment.

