**16. Confidentiality and data protection**

Personal data recorded on all documents will be regarded as strictly confidential and will be handled and stored in accordance with the Personal Data Protection Law (exposure draft). With the patient’s consent, their specify patient identifiers e.g. full name, date of birth, address, phone number and hospital number will be collected at trial entry to allow tracing through South China Liver Cancer Registries and to assist with long-term follow-up. Patients will be identified using only their unique trial number, initials (Pinyin), hospital number and date of birth on the Case Report Form and correspondence between the Trials Office and the participating sites. For trials collecting consent forms specify “However patients are asked to give permission for the Trials Office to be sent a copy of their signed Informed Consent Form which will not be anonymized. This will be used to perform in-house monitoring of the consent process”.

The Investigator must maintain documents not for submission to the Trials Office (e.g. Patient Identification Logs) in strict confidence. In the case of specific issues and/or queries from the regulatory authorities, it will be necessary to have access to the complete trial records, provided that patient confidentiality is protected.

The Trials Office will maintain the confidentiality of all patient’s data and will not disclose information by which patients may be identified to any third party other than those directly involved in the treatment of the patient and organisations for which the patient has given explicit consent for data transfer (e.g. laboratory staff). Representatives of the CORRECT trial team may be required to have access to patient’s notes for quality assurance purposes but patients should be reassured that their confidentiality will be respected at all times.

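### Section 3 ends follow-up at progression, which conflicts with overall survival as an endpoint; followed as written, it biases OS upward

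*Protocol*

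**What the plan says.** Section 3 (Design) holds the protocol's only rule on when follow-up of a patient ends: "After the treatment, the patients will be followed up until progression, death, or termination of the study for patient withdrawal".

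Section 2.3 makes OS a secondary endpoint, "defined as the time from the commencement of radiotherapy until death from any cause", with this censoring rule: "Patients who withdraw or are lost to follow-up or still alive will be censored at the date last known to be alive". Section 13.3 gives the method: "PFS and OS will be analyzed by the Kaplan-Meier method for all patients".

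Four other places bear on what happens after progression:

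- Section 4 schedules imaging, examinations, blood tests and adverse event recording. It has no contact for survival status.
- Section 10.1, Table 1, gives the time for the Follow-up Form as "Complete after each treatment cycle". The same table has a Death Form, filled in once the site hears of a death.
- Section 13.5 places the final analysis after every patient has been followed for at least 1 year.
- Section 16 collects identifiers, with consent, for tracing through liver cancer registries and "to assist with long-term follow-up".

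**The concern.** OS needs vital status after progression, because most deaths in this disease can be expected to follow progression. If contact stops at progression, the date last known alive for a progressed patient is about the progression date. Kaplan-Meier then treats that patient as having the same future risk of death as patients who have not progressed. That is informative censoring, and the curve comes to describe mainly deaths without prior progression.

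The OS estimate would be the one readers set beside the historical median OS of 11.7 months cited in Section 1.2. OS is also planned for log-rank comparisons by TMB, PD-L1 and microsatellite status (Section 13.3), and goes to the data monitoring committee each year with the other secondary outcomes (Section 13.4). An analysis plan cannot repair this later, because it cannot restore vital status that was never collected.

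**Working it through.** **The plan's own figure.** Section 13.6 gives 36 patients for 1-year PFS of 20% against 40%, two-sided 5%, 80% power, 10% loss. A one-sample normal approximation with the null variance gives (1.960 + 0.842)² × 0.2 × 0.8 / 0.2² = 31.4, so 32; 32 / 0.9 = 35.6, so 36. The figure reproduces, and it concerns PFS only. The protocol states no OS target, event count or power.

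**Step 1: how many patients the rule touches.** With 1-year PFS of 40% or 20%, 60% or 80% have progressed or died by 1 year. That is 0.6 × 36 = 21.6 to 0.8 × 36 = 28.8 patients. Section 3 stops following those who progress, while Section 13.5 expects a full year for all. The two cannot both hold for a patient who progresses within the year.

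**Step 2: what OS would read under the rule.** Assumptions not in the protocol:

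- PFS is exponential with 40% at 1 year, so the hazard is −ln(0.4) = 0.9163 per year.
- A share q of first PFS events are deaths without prior progression; range 10% to 30%.
- No death after progression is captured.

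Only deaths without progression then count, with hazard q × 0.9163, so the apparent 12-month OS is exp(−q × 0.9163).

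**Step 3: what true OS would be.** Add exponential survival after progression with hazard m per year. Its median is assumed to be 3.7, 6 or 12 months; the low end is the gap between the historical medians in Section 1.2, 11.7 − 8.0. With L = 0.9163, true 12-month OS is

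0.4 + (1 − q) × L / (m − L) × (0.4 − exp(−m)).

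Example, q = 0.2 and a median of 6 months: m = ln 2 / 0.5 = 1.386 and exp(−m) = 0.25, so OS = 0.4 + 0.8 × 0.9163 / 0.470 × 0.15 = 0.634.

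| q | Apparent 12-month OS | True, median 3.7 mo | True, 6 mo | True, 12 mo | Excess (points) |
| --- | --- | --- | --- | --- | --- |
| 0.1 | 91.2% | 58.2% | 66.3% | 77.0% | 14 to 33 |
| 0.2 | 83.3% | 56.2% | 63.4% | 72.9% | 10 to 27 |
| 0.3 | 76.0% | 54.2% | 60.5% | 68.7% | 7 to 22 |

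**Step 4: check by simulation.** A simulation of progression and death, with 24 months of accrual plus 12 months of follow-up, agrees. With q widened to 5% to 30%, true 12-month OS of 54% to 79% would read 76% to 96%, and true 24-month OS of 23% to 51% would read 58% to 91%. Among 36 patients, about 1.5 to 9 deaths would be counted instead of 17 to 27. The excess is in the same direction in every scenario; its size depends on the assumptions.

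**Step 5: do other sections supply the missing follow-up?** Section 8.2 says that patients who stop treatment are still followed as the protocol lays down, which leads back to Section 3. The Death Form waits for someone to report a death. Registry tracing depends on consent and has no stated timing, completeness or link to the OS analysis. If deaths arrive this way while survivors' last-alive dates stay at progression, deaths and survivors are ascertained unequally, and Kaplan-Meier is still not valid.

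**The case against.** The strongest reply is that Section 2.3 does not make progression a reason to censor OS. It censors at the date last known alive, and several places suggest that later deaths were meant to count: the Death Form is not tied to a treatment cycle, Section 16 provides for long-term tracing, Section 9.1.2.1 says that deaths from the cancer are recorded elsewhere on the case report form, and Section 13.5 expects a year of follow-up for all. The Section 3 sentence could then be meant for the disease-assessment phase only. This stands as evidence of intent. It does not supply a procedure, and the sentence does not say that it is limited to that phase. The result is a contradiction to reconcile, not a deliberate choice to abandon survival follow-up.

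Two stronger readings are tempting, and the protocol supports neither.

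- A reader might infer that OS cannot be validly estimated in this trial at all. That holds only for the follow-up rule as written. Sites may collect survival anyway.
- A reader might infer that the primary PFS is biased too, because Section 8.2 lists "Disease Progression (Radiological disease progression, Clinical disease progression" and a patient in clinical decline might leave imaging before a RECIST event. But that list gives reasons to stop the drug, not to stop scans. Section 4.1 says "Tumor response using contrast-enhanced computed tomography or magnetic resonance imaging should be performed every 6 weeks" without tying this to treatment, and Section 2.2 rests the primary endpoint on RECIST 1.1. No section says that scanning stops at clinical progression.

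It is also fair to say that the share of first events that are deaths, and survival after progression, are assumed, so the figures illustrate the bias and do not predict it.

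**Conclusion.** Section 3 is wrong as written. It conflicts with the OS definition in Section 2.3, the Kaplan-Meier analysis of all patients in Section 13.3 and the year of follow-up in Section 13.5. If it is followed and no later death is captured, OS is biased upward: under the assumptions in Step 2, 12-month OS would read about 91% to 76% regardless of survival after progression. The direction is firm under those conditions; the size is not.

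This should be fixed, but it does not threaten the trial's main result. OS is a secondary endpoint in a single-arm phase II trial with no OS hypothesis or decision rule, and neither the primary endpoint nor the sample size of 36 is shown to be affected.

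**What to change.** Reword Section 3 so that progression ends only the disease-assessment phase. State that vital status (date of death, or date last known alive) is actively collected for every patient after progression, by telephone, record check or registry, until death, withdrawal of consent or a common data cut-off. In Table 1, widen the Follow-up Form trigger so that it also covers survival follow-up after treatment.

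The cost is an amendment to the wording and a few contacts per patient for 36 patients. Consent for registry tracing is already sought. The sample size and the primary analysis stay as they are. The change is best made before follow-up of progressed patients lapses, since vital status missed then may be hard to recover.
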